## Methods

### Design

Study protocol for a randomized controlled parallel group single-blind trial. This study was registered with the International Standard Randomized Controlled Trial Number (ISRCTN30604244) and complies with the recommendations of The SPIRIT 2013 Statement.

Participants will be randomized to receive dry needling, either real or sham. Allocation to either group, namely real or sham dry needling, will be achieved through a computer-generated sequence of random numbers. The allocation sequence is created and carried out by a non-interventionist physiotherapist, in charge of telephone screening and of handling the data obtained in the various assessment sessions.

Figure 1 shows a flowchart of the progress of the various stages of this test. This study was approved by the Committee on Human Research, Universidad de Alcalá (Reference: CISM/HU/2015/19).

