### Randomization and blinding

At baseline, the non-interventionist physiotherapist, through the Random Allocation Software, will randomize by permuted blocks [4, 8], the participation of the 5 intervening physiotherapists with respect to a sample of 36 participants. The physiotherapist in charge of performing dry needling –which may be A (experimental) or B (control)- and 2 groups of 2 physiotherapists, G1 and G2, with an evaluator and a therapist in each group. 4 possible treatment groups (AG1, AG2, BG1, BG2) will be obtained evenly in each randomization block.

Participants who successfully pass the phone screening will be assigned a number on the randomization table in order of inclusion in the study; the treatment group (A or B) and physiotherapist group (G1 or G2) in which they will be included are specified. The physiotherapist responsible for carrying out the dry needling, will provide a list with the names of the participants, showing the type of intervention that each will receive (A or B).

Each participant will receive a single dry needling or sham dry needling intervention at the start of the first treatment session, conducted by a physiotherapist with more than 10 years of experience in MTrP treatment with dry needling. Said physiotherapist will be blinded to the baseline data of participants. On the other hand, both the physiotherapists who evaluate the participants and those who perform manual physiotherapy treatment and therapeutic exercise, will be unaware of the group of each participant.

In addition, data collected during the assessment of participants will not be revealed to the physiotherapists who perform the treatment, and participants will be instructed not to disclose their experience and information related to the first treatment session of dry needling.

Lastly, the physiotherapist responsible for the statistical analysis will be blinded. Once the intervention is finished he will receive a data table in excel with all the necessary data in binary code.

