### Statistical analysis

Data analysis will be carried out following the evaluation standards of the design of experimental studies with a control group. The experimental group (dry needling + manual physiotherapy and therapeutic exercise) will be compared with the control group (sham dry needling + manual physiotherapy and therapeutic exercise).

Data will be analysed using SPSS v.22 software for Windows. All statistical tests will be carried out considering a confidence interval of 95% (*p*-value <0.05) to determine the effectiveness of the 2 interventions by the method of intention to treat. Prior to statistical comparisons, all data will be analysed to determine the distribution of normality by the Shapiro-Wilk test. Subsequently, the homogeneity of the two intervention groups will be studied using Student’s t test for independent samples for data conforming to normal and the Mann-Whitney test for data that do not. The sex variable will be studied through Pearson χ2 or Fisher’s exact test, if the former cannot be used. Then a descriptive analysis of the data for the dependent variables will be performed. In these analyses, the mean and standard deviation (SD) for the dependent variables with normal distribution will be calculated. For variables that do not conform to normal, the data will be expressed with the median and first and third quartiles.

For the sex variable, frequencies are used. The existence of differences within each group will be determined, taking into account each group in isolation, between the different measurements (baseline and one week after dry needling; and post-treatment: at one week, at one month, at 3 months and at 6 months) in each of the study variables. In the VAS variable, measurements will also be taken in the treatment sessions; 2nd week, 3rd week, 4th week, 5th week, 6th week, using ANOVA for repeated measures, supplemented with simple and Helmert-type contrasts for variables that follow normal or Friedman’s ANOVA test, supplemented by Dunn’s multiple comparison test for those variables that will not conform to normal. ANCOVA will be performed to see the effect through different analyzes of the results and to intensify statistical power of the study. For this, the existence of a linear relationship and the homogeneity between the crude and basal scores of the dependent variables will be previously studied.

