For comparison between groups, a variable that we define as “difference” will be found; for each dependent variable, by subtracting the baseline measurement - at one week following needling, baseline - post 1 week, baseline - post 1 month, baseline - post 3 months and baseline - post 6 months (for the DASHe variable, the measurement will not be collected at one week after needling).

For the VAS variable, the “difference” variables will be found between baseline - week 2, week 3, week 4, week 5, week 6. To determine differences in dependent variables between the two intervention groups, the Student t test will be applied for related samples in variables whose data follow normal, in this case the effect size will be calculated according to the formula d = 2 t/√g. In the case of variables whose data do not follow normal, an analysis by the Mann-Whitney test will be performed and the effect size will be estimated according to Grissom procedures according to the formula.

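### The between-arm t test on change scores is specified for related samples, although the two arms are independent, unmatched patients

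*Protocol article*

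**What the plan says.** The Design section describes the trial as "Study protocol for a randomized controlled parallel group single-blind trial". Under Randomization and blinding, individual participants are allocated in permuted blocks; no matching of patients across arms is described. Under Sample size, 18 patients per arm are planned, with 25% allowed for losses.

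The Statistical analysis section forms change-from-baseline variables for the comparison of the arms. The purpose of the test that follows is given as "To determine differences in dependent variables between the two intervention groups", and the rule is that "the Student t test will be applied for related samples in variables whose data follow normal". The sentence continues: "in this case the effect size will be calculated according to the formula d = 2 t/√g". The symbol g is not defined. For the same comparison with non-normal data, "an analysis by the Mann-Whitney test will be performed".

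Three other statements in that section bear on the point:

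- Baseline homogeneity of the arms is checked with a "t test for independent samples for data conforming to normal".
- Repeated-measures ANOVA and Friedman's test are assigned to changes within each arm taken alone.
- An ANCOVA is planned after a check of linearity against baseline scores, but neither the comparison it serves nor its rank is stated. The analysis is declared to follow intention to treat.

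**The concern.** A related-samples t test works on differences within natural pairs, such as the same patient twice or two matched patients. Here each patient contributes one change score to one arm, and nothing links a patient on real needling to a particular patient on sham. The test therefore cannot be computed across arms until someone invents pairs, most likely by the order of rows in the data file. The result then depends on a choice that the protocol does not fix, and patients left without a partner drop out when the arms differ in size.

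What is at stake is the only rule explicitly attached to the between-arm comparison of normally distributed change scores, and VAS pain, the main outcome, is among the variables it covers.

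**Working it through.** **1. Do the passages agree?** Side by side:

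| Element | Where | Implies |
|---|---|---|
| Parallel groups | Design | independent arms |
| Permuted blocks, no matching | Randomization and blinding | independent arms |
| Mann-Whitney for the same comparison | Statistical analysis | independent arms |
| d = 2t/√g, if g is degrees of freedom | Statistical analysis | independent arms |
| t test for related samples | Statistical analysis | paired data |

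The last row stands alone. The baseline check uses the independent-samples t test for a different purpose. It does not contradict the last row, but it shows that the authors distinguish the two tests.

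**2. Degrees of freedom.** Input: n = 18 per arm, as stated under Sample size.

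- Independent samples: df = 18 + 18 − 2 = 34, two-sided 5% critical t = 2.032.
- Related samples on 18 invented pairs: df = 18 − 1 = 17, critical t = 2.110.

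**3. Dependence on row order.** Simulation: 200 data sets of 18 per arm, each with an independent-samples p between 0.045 and 0.055, and 400 random pairings of each. The paired p-value averaged 0.014 at the 2.5th percentile, 0.058 at the median and 0.11 at the 97.5th. Just under 40% of pairings fell below 0.05 and the rest did not, from the same data. This range applies only to data already near p = 0.05.

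**4. Type I error.** In 200,000 simulated trials with no treatment effect and arbitrary pairing of 18 with 18, the paired test rejected in 4.9%. The nominal 5% is kept.

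**5. Power.** With arbitrary pairs, the variance of a within-pair difference is 2σ². The noncentrality is d√(n/2) for both tests, and only the degrees of freedom differ. The values of d (difference in mean change divided by its SD) are assumptions.

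| d | Independent, df 34 | Arbitrary pairs, df 17 | Loss (points) |
|---|---|---|---|
| 0.5 | 30.8% | 29.4% | 1.5 |
| 0.8 | 64.5% | 61.9% | 2.6 |
| 1.0 | 83.0% | 80.7% | 2.3 |

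Losses are taken from unrounded values. With 14 per arm, the 28 patients that the protocol requires before losses, they are 1.5, 3.1 and 3.5 points.

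**6. Unequal arms.** As an illustration (assumed numbers), 12 and 16 completers would give 12 pairs. The test would use 24 of 28 patients and discard 4, contrary to the declared intention to treat.

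**7. Effect size.** Take d = 0.80 with 18 per arm, so t = 0.80 × √(18/2) = 2.40.

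- g = 34: 2 × 2.40/√34 = 0.82, close to the 0.80 that was put in.
- g = 17: 2 × 2.40/√17 = 1.16.
- g = 2 (number of groups): 2 × 2.40/√2 = 3.39, which is not credible and favours reading g as degrees of freedom.

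The ratio of the first two is √(34/17) = √2 = 1.41, an inflation of 41%. It arises only if g means degrees of freedom and the paired value of 17 is used.

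**The case against.** The strongest defence is that this is a slip of wording. The Mann-Whitney counterpart, the effect-size formula and the independent-samples test at baseline all suggest that independent was meant, and with no pairing rule an analyst would probably notice. That is plausible. It does not remove the point, because the sentence names the wrong test, nothing elsewhere in the article corrects it, and condensing a protocol into an article does not explain a misstated test.

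Four stronger readings might be inferred, and the document does not support them:

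- *That this is the trial's main test.* No primary test or time point is named. Non-normal data go to Mann-Whitney, and an ANCOVA is also planned.
- *That the effect-size formula is wrong.* It is the usual conversion for an independent-samples t with equal arms if g is degrees of freedom. The 41% depends on the conditions in step 7 of the working.
- *That the results would be biased towards dry needling.* Under arbitrary pairing the type I error is kept and a little power is lost. The outcome is arbitrary, not tilted.
- *That a before-after test within each arm is meant.* The sentence states a comparison of the arms on change scores, and within-arm changes have their own tests.

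**Conclusion.** The point holds in limited form. The protocol attaches a related-samples t test to the comparison of two independent, unmatched arms. The test is wrong for the design and inconsistent with its own non-normal counterpart, possibly through a slip.

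If it were run literally, the main harm would be an analysis that is not defined in advance: for borderline data the choice of row order could decide significance, and patients could be lost if arm sizes differ. The average statistical cost is small. The figures assume 18 per arm, pairs formed without regard to outcome, and standardised differences of 0.5 to 1.0, which the protocol does not state. The correction should be made before analysis because it settles which test is run and costs almost nothing, not because a large bias is expected.

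**What to change.** In the Statistical analysis section:

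1. Replace related samples with independent samples in the rule for the between-arm comparison.
2. Define g as the degrees of freedom of that test, n1 + n2 − 2.
3. State whether this t test or the baseline-adjusted ANCOVA already mentioned is the primary between-arm analysis.

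The cost is two or three sentences of wording, with no change to data collection, visits or sample size.

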### Sample size

The pain variable is chosen as the primary measurement of the study results. An effect size TE = 0.25 will be considered [21]. A correlation between repeated measures of 0.5 shall be assumed. Assuming the performance of 6 measurements -basal and a week after the dry needling, and post-treatment: at one week, at one month, at 3 months and at 6 months- in two treatment groups, sphericity correction will be determined at 0.5. With a statistical power of 0.95, with an alpha level of 0.05, a total sample size of 28 patients is estimated, and taking into account 25% for losses, a total of 36 patients needs to be reached, being 18 in both groups, using the Software Gpower 3.0.18 [22].

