### Primary outcome measures

The main result of this study will be the intensity of shoulder pain measured by ***Visual Analogue Scale (VAS) for pain***. Participants will mark the intensity of their pain on the VAS, consisting of a 100-mm long horizontal line, which is anchored by the classifications of “no pain” at the left end (score 0) and “worst pain imaginable” rightmost (score 10), asking to the participant for the most intense pain episode perceived meanwhile doing daily activity. The VAS has demonstrated the ability to detect changes in pain, establishing a minimal clinically significant difference at 13 mm [41, 42]. And in patients treated for rotator cuff disease a difference at 14 mm [43].

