***Strength in shoulder movements***. It will be measured with a hand dynamometer (microFET2® Hoggan Scientific LLC). The measurements will be taken in pounds and converted to kilograms-force. Strength in the following movements will be measured: flexion, abduction, external rotation and internal rotation.For measurements of isometric force in ER (external rotation) and IR (internal rotation), it has been found that the intraclass correlation coefficient (ICC) is 0.93 to 0.99. The minimum detectable change varies from 7.87 N (External Rotation) to 22.11 N (Internal Rotation) [48].The physiotherapist should stabilize manually or with straps the upper arm, shoulder, scapula and trunk, while performing the tests.Measuring the strength in flexion will be conducted with the participant in a sitting position with the shoulder at 45° of flexion and the elbow extended; the Dynamometer will be placed above the lateral epicondyle. The trunk will be strapped to avoid compensation [49]. Abduction will be carried out with the participant in a sitting position with 90° shoulder abduction, 90° elbow flexion and forearm neutral, positioning the dynamometer just proximal to the lateral epicondyle [50].Measurement of the internal rotation will be carried out with the participant supine; shoulder abduction, 90° elbow flexion and forearm neutral. The dynamometer will rest on the ventral side of the forearm, 2 cm proximal to the styloid process [48].For the measurement of external rotation, the participant supine; 90° shoulder abduction, 90° elbow flexion and forearm neutral. The dynamometer will rest on the back of the forearm, 2 cm proximal to the styloid process [48].While performing the baseline measurement, data for secondary outcome measures of the participant’s healthy side will also be collected in order to establish whether there is a baseline difference between the two sides before starting the intervention.

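### The only between-arm effect measures named are unitless (d from change scores, or a Grissom index), although relevance is defined as 13-14 mm VAS and 10.2 DASHe points; no difference with a confidence interval is named

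*Protocol article*

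**What the plan says.** All references are to the protocol article.

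- **Variable compared (Statistical analysis).** "For comparison between groups, a variable that we define as" a difference, formed as baseline minus each later measurement.
- **Test and effect measure, normal data (same section).** "the Student t test will be applied for related samples in variables whose data follow normal", and "in this case the effect size will be calculated according to the formula d = 2 t/√g". The symbol g is not defined; I read it as degrees of freedom.
- **Effect measure, non-normal data (same section).** After a Mann-Whitney test, "the effect size will be estimated according to Grissom procedures according to the formula".
- **Other summaries (same section).** Means and SDs of the outcomes are planned, or medians and quartiles where normality fails. The 95% level is attached to the tests. An ANCOVA is mentioned, but no reported estimate is assigned to it.
- **Relevance thresholds.** For the VAS, Primary outcome measures cites work "establishing a minimal clinically significant difference at 13 mm" and adds that "in patients treated for rotator cuff disease a difference at 14 mm". Secondary outcome measures gives 10.2 points for the DASHe.
- **Planning assumption (Sample size).** "A correlation between repeated measures of 0.5 shall be assumed", with a sphericity correction of 0.5. No SD for the VAS is given.

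**The concern.** The trial gives one needling session and follows patients to 6 months after treatment. Its readers will ask two things: is the pain benefit large enough to matter, and does it last? The article sets its standard for the first in millimetres and DASHe points, then fixes effect measures that carry no unit.

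The second question is affected as well. A d built from change scores divides the benefit by the SD of change at that visit. It can therefore move between visits for reasons unrelated to the benefit. If one visit passes the normality check and the next fails it, the two results are not even on the same scale. With groups this small, a point value of d and a p-value also hide how wide the range of compatible benefits is.

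**Working it through.** The article gives no numerical effect estimate to reproduce, so the check concerns what the stated formula does.

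**Inputs from the article:** 18 per arm as planned; 28 in total before allowance for losses, so 14 per arm; correlation 0.5; thresholds 13 and 14 mm.

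**Assumptions:** VAS SD 20 mm (15-25 mm as a range); correlations other than 0.5; g as degrees of freedom; an independent-groups t.

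**Step 1: what the formula measures.** For arm difference D, SD of change s and n per arm, t = D / (s√(2/n)). Then 2t/√df = (D/s) × √(2n/df), with df = 2n − 2. The last factor is √(36/34) = 1.029 at 18 per arm and √(28/26) = 1.038 at 14 per arm. So d is essentially D divided by the SD of change, and the unit cancels.

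**Step 2: d at the article's own correlation.** With equal SDs at both visits, s = SD × √(2(1 − r)). At r = 0.5 this gives s = SD. A 13 mm benefit then gives 13/15 = 0.87, 13/20 = 0.65 or 13/25 = 0.52 for SDs of 15, 20 and 25 mm. The value is the same at every visit. Which d corresponds to the relevance threshold depends on an SD that the article does not state.

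**Step 3: d when the variance of change differs between visits.** For a constant 13 mm, with baseline SD 20 mm and s = √(SD₀² + SD₁² − 2r·SD₀·SD₁):

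| r | follow-up SD (mm) | s (mm) | d |
|---|---|---|---|
| 0.7 | 20 | 15.5 | 0.84 |
| 0.5 | 20 | 20.0 | 0.65 |
| 0.3 | 20 | 23.7 | 0.55 |
| 0.5 | 15 | 18.0 | 0.72 |
| 0.3 | 12 | 20.0 | 0.65 |

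The same benefit can give a lower, higher or unchanged d. The rows only illustrate this; apart from r = 0.5, their inputs are assumed.

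**Step 4: precision.** The 95% CI half-width is t(0.975, 2n − 2) × s × √(2/n). With s = 20 mm:

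- 18 per arm: 2.032 × 20 × 0.333 = 13.5 mm
- 14 per arm: 2.056 × 20 × 0.378 = 15.5 mm

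Over s = 15-25 mm the range is 10.2-16.9 mm at 18 per arm and 11.7-19.4 mm at 14 per arm. An observed difference equal to the 13 mm threshold would, at s = 20 mm, have an interval from just below zero to about 26 mm (18 per arm).

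**The case against.** The strongest reply has four parts.

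- **A flat d.** The article assumes a single correlation of 0.5, which with equal SDs keeps d constant for a constant benefit (step 2). A reader might infer that the formula would make a lasting benefit appear to fade. The documents do not support that. It needs a correlation with baseline that falls over follow-up and follow-up SDs that do not offset the fall, and the article states neither. The sphericity correction of 0.5 does imply unequal variances among between-visit differences. It does not say which way they move, or even that the baseline-to-visit differences are the ones affected. This part stands against the fading claim, but not against the fact that d is tied to a visit-specific SD.
- **A difference in mm can be derived.** A reader might also infer that the results could not be set against the thresholds at all. That is too strong. The planned means and SDs give a point difference for normal data, and the ANCOVA could supply one. Medians and quartiles, however, do not yield a between-arm shift with an interval, and no such estimate is named for reporting.
- **A condensed article leaves reporting detail elsewhere.** This would count if the section were silent. It is not: it names the effect measures and gives a formula for d. The point concerns a stated choice.
- **Unit mismatches are trivial.** This is correct. The VAS line is 100 mm scored 0 to 10, so 13 mm is 1.3. For strength, "The measurements will be taken in pounds and converted to kilograms-force" while the cited limits are in newtons, which is a fixed conversion.

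**Conclusion.** The concern holds in a limited form. The between-arm effect measures that the article names are unitless, change scale if a visit fails the normality check, and cannot be read directly against 13-14 mm VAS or 10.2 DASHe points. The d can differ between visits for the same benefit in mm if the variance of change differs, in a direction that the documents do not fix. Neither d nor the p-value shows that the interval around a VAS difference is likely to be about as wide on each side as the threshold: 13.5-15.5 mm with 14-18 per arm and an assumed SD of change of 20 mm.

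The figures rest on assumed SDs and an independent-groups t. If the paired form named in the text were actually run, 2t/√df would be about twice a standardised mean change and not a between-arm effect; that label is a separate matter. This should be changed, but it does not in itself invalidate the planned comparisons.

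**What to change.** In Statistical analysis:

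- Make the reported between-arm effect at each visit the mean difference in original units with its 95% CI, from an independent-groups comparison. Where Mann-Whitney is used, report the Hodges-Lehmann shift with its CI.
- Express the VAS in mm. Interpret the VAS against 13-14 mm and the DASHe against 10.2 points.
- Do not judge group differences in range of motion, pressure pain threshold or strength against the figures quoted for them. Those are real-change or minimum detectable change limits, not relevance thresholds for a group difference, and for strength they cover the two rotations only.
- Keep d only as a supplement, and define g.

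The cost is a change of wording, with the same data and visits. The downside is that the intervals will look wide.
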